#### 2.4.1. Inclusion in Groups

The first week will allow us to include patients with left USN and to randomly assign them to four independent parallel groups (centralized randomization in a 1:1 ratio performed using a custom made algorithm on Matlab (MathWorks, Inc., Natick, MA, USA) by a blinded investigator: a control group receiving no additional treatment to conventional occupational therapy sessions and three experimental groups receiving in addition to the usual treatment either left-NMV, left-NMV + sham-tDCS or left-NMV + a-tDCS experimental treatments, administered by trained occupational therapists.

In these three experimental groups, each patient will be equipped with vibratory stimulators during conventional occupational therapy sessions taking place on Monday, Wednesday and Friday for three weeks from the second week on. The left-side NMV vibrator will be activated during the first 15 min of the occupational therapy session (lasting 45 min), as previously described [21,35]. In the two experimental groups receiving sham or a-tDCS, electrodes will be placed as described above. A continuous 2 mA current will be delivered for 20 min in the left-NMV + a-tDCS group, 5 min before (patients will be seated in a quiet room) and during the first 15 min of the occupational therapy session, simultaneously to the NMV stimulation. The current will be automatically turned off after 20 s in the left-NMV + sham-tDCS group, allowing the reproduction of the initial mild itching sensation at the beginning of active tDCS, thus ensuring that the patient stays blind to the activation status of the device. In the case of adverse events or unintended effects of trial interventions, the investigator who enrolled the patient will report its occurrence to the trial sponsor through a report form provided in the case report form.

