The Wheelchair navigation test [21], illustrated in Figure 3, aims at investigating spatial navigation skills and extra-personal neglect. The ride will be carried out once in each direction (A-B and B-A) to balance the number of obstacles and turns to the left and right. The time taken to finish the course will be measured and the number of bumps counted. Navigation quality will also be observed qualitatively (obstacle avoidance, goal strategy, perseverations).

Each test will be carried out several times over the study by a trained occupational therapist:

Baseline assessment (Pre): During the first week, each test (except for the CBS realized only once) will be repeated three times in order to obtain a reliable estimation of the participants’ performance level (mean values) before starting the experimental interventions.

Follow-up assessments: These will take place just at the end of the first experimental session (Postsession1), after the first and third weeks of the protocol (Postweek1 and Postweek3, respectively) and there will be a final evaluation three weeks after its ending (Postweek6). In addition, all patients will be asked about their expectations and satisfaction regarding the treatment at the end of each week of intervention.

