### 2.5. Sample Size Calculation

To determine the number of left USN patients to include, we sought to perform an a priori headcount calculation based on published work in the field. However, none of them have combined NMV and tDCS or used the CBS score as the primary endpoint. No a priori power calculation could therefore be performed, but we were inspired by the number of patients included in the works of Làdavas et al. [32] and Turgut et al. [33], both of whom used tDCS on USN patients, the former combined with visual prisms and the latter with optokinetic drift. These two studies included 30 and 32 patients, respectively, which were divided for the first in two groups of 11 patients and one group of 8, and for the second in two groups of 16 patients. Thus, we estimated that 48 patients would be necessary for our study, randomly and homogeneously distributed in each of the 4 groups. To ensure that the target number of patients is recruited, three neurological rehabilitation centers admitting each year a large number of patients meeting the inclusion criteria will be involved. We will verify a posteriori that the groups do not differ in sex, mean age, education, duration of illness, or baseline CBS scores, and that they have similar stroke locations.

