### 2.6. Statistical Analysis

CBS scores, those of personal neglect, mean egocentric errors and mental evocation, the time needed to finish the wheelchair course and the number of bumps in each direction will be entered as quantitative data.

After having verified the required assumptions about data distributions (Shapiro–Wilk test of normality, Levene’s test of homoscedasticity, Box’s M-test of covariance homogeneity and Mauchly’s test of sphericity), a mixed analysis of variance (with repeated measures for the SSA) will be performed on each quantitative variable with test periods (Pre, Postsession1, Postweek1, Postweek3, Postweek6) as within-subject factors and treatment groups (control, left-NMV, left-NMV + sham-tDCS, left-NMV + a-tDCS) as between-subject factors. Post hoc tests will be conducted using Tukey’s honestly significant difference method when needed, and *p*-values will be adjusted with the Bonferroni method. Size effects will be reported using the η2 (Eta-square) for each ANOVA and Cohen’s d for each Tukey’s post hoc test, along with confidence intervals.

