If the conditions for using parametric tests are not met, then non-parametric statistical analyses of comparisons between test periods and groups will be performed. For each treatment group, we will perform a Friedman test to analyze the effect of the test period on each quantitative variable independently. When a Friedman test is significant, post hoc Wilcoxon signed rank tests with the Bonferroni adjustment method will be used to perform pairwise comparisons between each of the five time points. Kruskal–Wallis tests will be performed to compare the treatment groups. First, a Kruskal–Wallis test will be performed on the sum of ranks of the scores in each group before the first session in order to ensure that the initial mean scores (Pre) are equivalent between groups. Second, the effect of treatment will be calculated for each participant at each post-session assessment (Postsession1, Postweek1, Postweek3, Postweek6) by subtracting the mean initial score (Pre) from each quantitative data, independently. In order to analyze the effect of the treatment received on the evolution of quantitative data, Kruskal–Wallis tests will be performed on the sum of ranks of the Post–Pre score differences in each group. When the Kruskal–Wallis test is significant, post hoc pairwise comparisons between groups will be calculated, and the *p*-value will be adjusted by the Steel–Dwass–Critchlow–Fligner method.

Any participant with a missing score on any of the assessment sessions will be excluded from the statistical analysis for that specific test.

All statistical analyses will be performed using R software (version 2021.09.1 Build 372). The threshold for statistical significance will be set at α = 0.05.

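### Missing any one of five assessments removes a participant from an outcome's whole analysis, primary outcome included; observed scores are lost and randomisation no longer protects the analysed set

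*Protocol article*

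**What the plan says.** Section 2.6 gives one rule for missing data: "Any participant with a missing score on any of the assessment sessions will be excluded from the statistical analysis for that specific test". The main analysis is a mixed ANOVA by treatment group "with test periods (Pre, Postsession1, Postweek1, Postweek3, Postweek6) as within-subject factors", so five scores must be present. The last comes late: "a final evaluation three weeks after its ending (Postweek6" (section 2.4.3). The rule makes no exception for the primary outcome, the evolution of the CBS score.

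If parametric assumptions fail, section 2.6 compares the groups by Kruskal–Wallis tests on the change from Pre at each follow-up. The exclusion sentence comes after that paragraph and covers it too.

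On size, section 2.5 says: "Thus, we estimated that 48 patients would be necessary for our study, randomly and homogeneously distributed in each of the 4 groups". It also says: "No a priori power calculation could therefore be performed". The article states no expected missingness, analysis by assigned group, imputation or sensitivity analysis that would offset the rule.

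**The concern.** This is a fixed analysis choice, not a detail left to an unseen analysis plan. It has two consequences.

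- **Waste.** All of a patient's scores on an instrument go when one is missing. A missed Postsession1 CBS removes the observed Postweek3 and Postweek6 CBS, which bear most directly on lasting recovery.
- **Loss of protection.** Who is analysed depends on what happens after randomisation. Complete-case analysis is safe in general only if scores are missing completely at random. Missed assessments are foreseeable here: patients are sub-acute, consent can be withdrawn at any time, and the last assessment falls three weeks after the intervention ends.

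At stake are the precision of an already small trial and, under some patterns of loss, the validity of the primary group comparison.

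**Working it through.** **Inputs from the article.** 48 patients in 4 equal groups, so 48/4 = 12 per group; 5 periods (Pre plus 4 follow-ups); α = 0.05, taken as two-sided. The 48 does not come from a power formula. It is in line with the groups in the two cited trials: (11 + 11 + 8 + 16 + 16)/5 = 12.4.

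**Assumption.** The article gives no missingness rate. I take a rate m at each of the four follow-ups, independent between visits, with Pre always present.

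**Step 1: patients kept.** Expected complete cases = 48 × (1 − m)^4. Scores observed = 48 × (5 − 4m). Scores kept = 5 × complete cases.

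| m | Fraction complete | Patients kept of 48 | Per arm | Observed scores discarded |
|---|---|---|---|---|
| 3% | 0.885 | 42.5 | 10.6 | 234.2 − 212.5 = 21.8 |
| 5% | 0.815 | 39.1 | 9.8 | 230.4 − 195.5 = 34.9 |
| 10% | 0.656 | 31.5 | 7.9 | 220.8 − 157.5 = 63.3 |

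Independence is close to the worst case for a given rate. At the other extreme, if the same patients miss every follow-up, 48 × (1 − m) = 46.6, 45.6 or 43.2 remain.

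**Step 2: precision.** Consider one unadjusted pairwise contrast with an assumed standardised difference of 1.0. Power = Φ(1.0/√(2/n) − 1.96).

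- n = 12: Φ(2.449 − 1.96) = 68.8%
- 10% incomplete, n = 10.8: Φ(2.324 − 1.96) = 64.2%
- 20% incomplete, n = 9.6: Φ(2.191 − 1.96) = 59.1%
- 30% incomplete, n = 8.4: Φ(2.049 − 1.96) = 53.6%

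The 68.8% assumes no missing data. A model using all observed scores recovers part of the gap, not all of it.

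**Step 3: bias in the planned contrast.** A simulation with 200,000 patients per arm used five visits, SD 1, correlation 0.7 between all visits and no true effect. Lower scores meant better. Postweek6 missingness depended on the observed Pre-to-Postweek1 change. The measure was the between-arm difference in change from Pre, as in the plan.

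| Missingness | Complete cases, Postweek3 | Complete cases, Postweek6 | Likelihood, Postweek6 |
|---|---|---|---|
| 20% in both arms, completely at random | 0.00 | 0.00 | 0.00 |
| 20% in both arms, non-improvers leave | 0.00 | 0.00 | 0.00 |
| Non-improvers leave: control 10%, active 30% | −0.08 | −0.08 | 0.00 |
| 20% each: control improvers, active non-improvers leave | −0.18 | −0.18 | 0.00 |

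Every Postweek3 score was observed in these runs. The Postweek3 bias arises only because the rule discards them.

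For scale, the SD of change is √(2 × (1 − 0.7)) = 0.775, so the standard error with 12 per arm is 0.775 × √(2/12) = 0.32. The biases of 0.08 and 0.18 are about a quarter and just over half of one standard error.

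**The case against.** **The rule follows from the method.** Repeated-measures ANOVA and the Friedman test need complete rows. That explains the rule for those two methods, but it does not justify it for the Post–Pre Kruskal–Wallis comparisons, and a mixed model removes the need in the main analysis.

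**The losses may be small.** The rates are assumptions. Dropout is often monotone, Postsession1 is taken at the end of a session the patient is already attending, and the article places each patient's participation within seven weeks of rehabilitation. These points stand: the lower end of the loss range is as plausible as the upper.

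**Bias is not certain.** A reader might infer that the primary comparison is biased whenever leaving relates to recovery. The simulation does not support that: with the same mechanism in both arms and no true effect there was none. With a true effect and missingness driven by Postweek3, a raw Postweek6 mean difference can look clearly attenuated. The plan does not use that contrast, however. It analyses change from Pre, and under equal correlation between visits the selection shifts Pre and Postweek6 alike and cancels at Postweek6. The cancellation is not general: it fails at Postweek3 in that setting, and at Postweek6 under autoregressive correlation.

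**Wheelchair test.** A reader might also infer that patients who cannot finish the course are deleted, since "The time taken to finish the course will be measured and the number of bumps counted". The article does not say how non-finishers are scored, and the full protocol may do so. I make no claim on it.

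**Wording.** The phrase about a specific test could mean a statistical test. The article uses the word for its neglect instruments, and the sentence refers to assessment sessions, so the instrument reading is the natural one.

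**Conclusion.** The point holds as an avoidable weakness that should be fixed before analysis. It does not invalidate the trial, and no stated power is contradicted because none is stated. Certain from the text: the rule discards observed scores, applies to the primary outcome, and defines the analysed set by post-randomisation events. Conditional: its size. Under independent missingness of 3% to 10% per follow-up, about 42 to 31 of 48 patients remain; with fully overlapping missingness, about 47 to 43. Under missing completely at random only precision is lost. Bias requires missingness related to outcome, together with a difference between arms or a contrast in which the selection does not cancel. In the arm-dependent scenarios examined it was 0.08 to 0.18 SD. Those figures rest on an assumed correlation of 0.7 and assumed dropout patterns, and are illustrations, not predictions.

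**What to change.** Replace the exclusion sentence in section 2.6 with:

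> All randomised participants are analysed in the group to which they were assigned, using all observed scores, in a mixed model for repeated measures valid under missing at random, with group, post-baseline period (Postsession1, Postweek1, Postweek3, Postweek6), group × period and the Pre score as covariate, unstructured covariance (a simpler structure if it does not converge) and Kenward–Roger degrees of freedom; complete cases are a sensitivity analysis.

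Pre is then a covariate only and must leave the period factor, so the mixed-ANOVA sentence and its assumption checks need matching edits.

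In the non-parametric fallback, include in each Post–Pre Kruskal–Wallis comparison every participant with those two scores. The Friedman test still needs complete rows, but it is a within-group analysis.

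Cost: rewording of the analysis section, a little more analysis work in R, which is already the chosen software, and a model with more parameters at 12 per arm; hence the simpler covariance as a stated back-up. No extra patients or data are needed. Participants with no follow-up score still contribute nothing to the model, so their number and reasons should be reported by arm.

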### 2.7. Dissemination Policy

Patients will have the option of knowing their personal results and/or the results of the study after publication. The anonymous results of this research will be disseminated in internal communications, scientific conferences and published in scientific journal articles.

## 3. Discussion

The rehabilitation of spatial cognition disorders, such as the USN syndrome, is still a real challenge, which is partly due to the associated anosognosia and attentional disorders [8]. The HEMISTIM protocol may represent a partial solution by proposing an innovative therapeutic approach based on well-identified tools accessible to therapeutic teams. The aim of this protocol is to optimize conventional USN rehabilitation practices through the contribution of new scientific knowledge in the fields of neuromodulation and spatial cognition and more particularly the interest of augmented sensory feedback in spatial perception. In this respect, our previous translational research studies have addressed this question and identified the optimal sensori-motor context for the persistence of left-side NMV effects [35] and its benefits in a USN case study [21].

The perceptual effects of NMV are attributed to a non-specific activation of the contralateral hemisphere and the activation of vestibular neurons in the parieto-insular cortex [42]. These neurons with bilateral receptive fields participate in multisensory integration processes and internal representations of the position of the head and body in space [42]. Left-side NMV seems to counterbalance the egocentric representation deviation observed in USN patients through these central mechanisms [43]. The key question of persistent effects was addressed by Ceyte et al. [35], who showed that lasting post-effects were only present when left-side NMV was associated with upper limb self-activation, and these results were consistent with our previous case study on a USN patient [21]. Transferring our protocol directly into conventional rehabilitation sessions could further increase their benefits. Indeed, reaching toward a target, as it was performed in a visuo-haptic feedback context in our previous studies [21,35], is very similar to the motor activities performed during ecological upper limb rehabilitation sessions. Based on these findings, we assume that using this technique during occupational therapy sessions might enhance beneficial effects obtained by conventional rehabilitation without needing to add specific sessions as it is sometimes suggested. In addition, the positive impact expected from this initial protocol could be optimized by tDCS neuromodulation. Indeed, non-invasive brain stimulations are known to modulate cortical excitability and therefore seem an ideal tool to promote long-lasting neuroplasticity [44]. The duration, amplitude and polarity of excitability changes vary accordingly to current flow direction, current intensity and stimulation duration [45]. Neuronal excitability changes induced by tDCS are supposed to be mediated by processes which are similar to long-term potentiation (LTP) and depression (LTD), among others [45]. These neurobiological mechanisms could significantly favor the intermodal recalibration induced by our initial protocol [35,46]. Interestingly, neurobiological post-effects can be observed during minutes and up to several hours after the end of tDCS stimulation [47,48]. Lasting clinical benefits on USN were also shown [28,31] but not consistently, due in part to substantial protocol differences (stimulation duration and repetition, concurrent activity, time since brain lesion). This technique has already been used simultaneously to occupational therapy sessions with positive and lasting results [28]. Moreover, its association with “bottom–up” rehabilitation approaches is very promising in terms of potentiating their beneficial impact on USN [32,33]. Associating tDCS with our initial protocol therefore seems perfectly suited to attempt to induce or reinforce LTP-like activity-dependent plasticity and consequently lasting intermodal recalibration to improve clinical aspects of USN.

There are some inherent features of our study protocol that deserve cautious consideration. Particular attention will be directed to the phenomena of limb activation and motor extinction [36,37], since our protocol is designed around the performance of voluntary upper limb movements simultaneously to stimulation sessions in USN patients. Although it has been shown in the literature that the use of the contralesional arm in the neglected hemi-space significantly reduces the severity of USN [37], these patients generally have great difficulty in mobilizing it in the early post-stroke stages. Moreover, the simultaneous use of both upper limbs in the neglected hemi-space limits or even suppresses the previously observed beneficial effects [36,37] possibly by perceptual “overshadowing” of the contralesional arm movements by the ipsilesional ones, according to Robertson and North [37]. Therefore, the therapists will carefully avoid bimanual activities in the neglected hemi-space, but exercises will be allowed with the right upper limb instead of the left one if the latter is too impaired to effectively perform them in initial phases of rehabilitation. This gradual increase in task complexity is also intended to maintain high motivation levels. Other vigilance points will be taken into account. We will be watchful of population homogeneity, hence the need to include a sufficient number of patients. We will compare the evolution of each patient from baseline according to his affiliation group, given the possibility of inter-subject variability in responsiveness. In addition, the long-term effects of tDCS should be clarified, and its optimal targets for motor and spatial rehabilitation have not been sufficiently studied yet. There is also a risk of misuse or overuse of non-invasive stimulations. Finally, local rehabilitation teams will be coordinated for inter-site standardization of inclusion, occupational therapy tasks, test performance and stimulation tools use.

In conclusion, the originality of our study lies in this novel combination of non-invasive stimulation techniques with low attentional demands and their application during occupational therapy sessions, thus ideally complementing conventional rehabilitation. The results of our multimodal approach should also provide interesting data to reconsider hemi-spatial theories suggesting a dominant function of the right hemisphere or others supporting an “interhemispheric competition” model [49].

## Figures and Tables

**Figure 1 brainsci-13-00678-f001:**

HEMISTIM protocol design. Red circle symbols indicate experimental sessions. Assessment periods are indicated by vertical arrows.

**Figure 2 brainsci-13-00678-f002:**
[figure not shown]
(**a**) Topographical displacement of the stickers in the Fluff test. Numbers indicate target locations; (**b**) Gainotti’s drawing copying test; (**c**) Spatial benchmarks of the map of France; (**d**) Experimental device for the Subjective Straight-Ahead test.

**Figure 3 brainsci-13-00678-f003:**
[figure not shown]
Example of wheelchair navigation course taken from Ceyte et al. (2019) [21].

## Data Availability

No new data were created or analyzed in this study. Data sharing is not applicable to this article.
